##### Evaluation

Patient-level data from the optional, anonymous online survey will be clustered by site. Once a site has secured five survey responses, data will be collated and presented on the SHAIR Collaborative website’s feedback dashboard. Individual site data will be reported to sites, at request.

#### Adoption

##### Data collection

Our main measure of adoption is the total number of SHAIR Collaborative sites that actively participate. Sites that are interested in joining the SHAIR Collaborative will sign a letter of support. We will note when sites join the SHAIR Collaborative and if they become inactive (based on lack of responsiveness or signaling their resignation). We will recruit additional sites routinely throughout the project guided by stakeholder feedback.

Additionally, we will conduct brief interviews with SHAIR site champions (clinical and non-clinical) approximately 1 year into implementation and again towards the end of the formal implementation period before sustainability. The interview guide will be designed using Diffusion of Innovation and other relevant frameworks [25]. Interviews will be first conducted with phase 1 sites and then phase 2 sites, as relevant.

Lastly, we will measure social interconnectedness within SHAIR Collaborative over time utilizing quarterly online surveys to active SHAIR Collaborative members. The surveys will include identifying names and the number of contacts made within the Collaborative [38].

##### Evaluation

We will report the number of active SHAIR sites and the number of those that became inactive at the conclusion of the project funding period. We will also report the proportion of all sites that join the SHAIR Collaborative and are still active at the conclusion of the project funding period.

The site champion interviews will be conducted using an interview guide designed in collaboration with project stakeholders and informed by implementation progress. The interviews will be audio-recorded and conducted by one team member while another team member will take notes during each interview. Two independent reviewers will review the interviews and conduct qualitative analysis. A third individual will be available to arbitrate, if necessary.

We will use regression analysis to assess the impact of social interconnectedness within the collaborative over time on the primary outcome of site-level patient reach [39].

#### Implementation

##### Data collection

To assess the extent to which the conversation aids are normalized at phase 1 sites, we will use the unadapted Normalization MeAsure Development (NoMAD) instrument [40]. NoMAD is a 23-item questionnaire designed to evaluate implementation processes according to Normalization Process Theory [41]. Our primary contact at each phase 1 site will identify eligible individuals and provide them with an anonymous Qualtrics link to survey. The survey will include an information sheet, three questions about the respondent’s site, role, and years of experience, and then each section of NoMAD. We will ask our primary contacts to include clinical and non-clinical roles that may be involved in the implementation of the conversation aids. We will ask them to distribute the NoMAD survey three times: prior to implementation, halfway through the implementation project period, and at the end of the implementation project period.

We will use an expanded framework for reporting adaptations and modifications to evidence-based interventions (FRAME) to document changes to the early-stage breast cancer conversation aids [42]. We will use a framework for documenting modifications to implementation strategies in healthcare (FRAME-IS) to document changes to our implementation strategy [43].

We will collect a range of SHAIR Collaborative and implementation facilitating factors on a monthly and quarterly basis (see Table 1). Each factor is based on our implementation approach and will be assessed based on how often sites engage in each factor. We will complete assessments as a team using logs from the month or quarter to input the values for that time period for each site.

**Table 1 Tab1:** List of implementation facilitating factors

Factor	Rating approach	Notes/scoring
**Monthly**		
Communications engagement	Yes/no	**• Yes** = communicated with us at least 1 in a given month (e.g., emailed back with patient uses) **• No** = did not communicate with us in a given month
Dashboard development	Yes/no	**• Yes** = Pt surveys collected **• No** = Pt surveys not collected
Website engagement	Yes/no	**• Yes** = downloaded something on website or engaged via comments on website **• No** = did none of those
Other notes on site’s engagement	N/A	

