## Abstract

**Background:**

Shared decision making (SDM) in breast cancer care improves outcomes, but it is not routinely implemented. Results from the What Matters Most trial demonstrated that early-stage breast cancer surgery conversation aids, when used by surgeons after brief training, improved SDM and patient-reported outcomes. Trial surgeons and patients both encouraged using the conversation aids in routine care. We will develop and evaluate an online learning collaborative, called the SHared decision making Adoption Implementation Resource (SHAIR) Collaborative, to promote early-stage breast cancer surgery SDM by implementing the conversation aids into routine preoperative care. Learning collaboratives are known to be effective for quality improvement in clinical care, but no breast cancer learning collaborative currently exists.

Our specific aims are to (1) provide the SHAIR Collaborative resources to clinical sites to use with eligible patients, (2) examine the relationship between the use of the SHAIR Collaborative resources and patient reach, and (3) promote the emergence of a sustained learning collaborative in this clinical field, building on a partnership with the American Society of Breast Surgeons (ASBrS).

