#### Reach

##### Data collection

Our primary outcome is patient reach, which is defined as the number of patients who are given the opportunity to use one of the conversation aids over the number of eligible patients, by site. Surgeons using the conversation aids at each site will determine patient eligibility based on clinical judgment. We will determine patient reach for each site on a monthly basis using the following data:Reported uses of the conversation aids—We will email each site monthly to request data and notes for the previous month regarding patient reach. Other uses of the conversation aids can include using paper copies, sending links or PDFs to patients by email, patient portal, EHR, or other distribution methods.From our experience, we anticipate that paper versions will be used only once with patients [11]. However, we realize a patient may be given multiple copies throughout their care and/or for others to view (family members, friends, caregivers). While this may occur, we do not anticipate our sites to regularly provide multiple paper copies of an Option Grid/Picture Option Grid. In the instance multiple copies are given, we will work with each site to try and get as accurate of count as possible.Online access to conversation aids via platform—The SHAIR Collaborative website is able to track the downloads of the conversation aids or clicks out to the linked EBSCO website for the interactive tools. Downloads will be tracked and reported on a monthly basis.

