##### Evaluation

We will calculate descriptive statistics summarizing the NoMAD survey results for each phase 1 site at the conclusion of the implementation period.

Separately, we will use the factors shown from Table 1 as variables in a linear regression analysis to explore which factors might be associated with high levels of patient reach (clinical championship, team engagement, communications engagement etc.) and therefore might predict future patient reach. For these regressions, patient reach will be the dependent variable and each implementation factor will be an independent variable. We will assess each item at the site level so that “site” will be the unit of analysis. We will control for patient demographics and other potential sources of site heterogeneity, if possible.

Additionally, we will conduct mixed-effects linear or logistic regression analyses to examine the association between these implementation factors and our patient-reported outcomes. We will conduct an analysis for each outcome while controlling for patient demographics as fixed effects. For this analysis, “patient” will be the unit of analysis but we will account for clustering at the site level as a random effect.

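### Two monthly Table 1 factors partly contain the events from which reach is measured, so the exploratory regression of reach on them can show an association without any true effect

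*Protocol article*

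**What the plan says.** The second aim in the Abstract is to "examine the relationship between the use of the SHAIR Collaborative resources and patient reach". Reach is aids offered over eligible patients, by site and month. The Reach section (Data collection) names two sources:

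- The site's report: "We will email each site monthly to request data and notes for the previous month regarding patient reach".
- Online access: "The SHAIR Collaborative website is able to track the downloads of the conversation aids or clicks out to the linked EBSCO website".

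Under Reach (Evaluation), both are counted for each site every month.

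The Implementation section (Table 1, monthly factors) scores each site Yes or No on three items:

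- Communications engagement is Yes if the site "communicated with us at least 1 in a given month (e.g., emailed back with patient uses".
- Website engagement is Yes if the site "downloaded something on website or engaged via comments on website".
- Dashboard development is Yes if "Pt surveys collected".

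In Implementation (Evaluation), "patient reach will be the dependent variable and each implementation factor will be an independent variable", with the site as the unit of analysis. The same section adds that "we will conduct mixed-effects linear or logistic regression analyses to examine the association between these implementation factors and our patient-reported outcomes".

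**The concern.** A predictor should not be scored from the event that produces the outcome. Here the reach reply is the stated example of communications engagement, and an aid download satisfies website engagement while also being listed as reach data. A positive coefficient could then reflect how reach was recorded and not what engagement achieves. The Discussion intends these results to show which engagement factors affect implementation success, so an artefact could be carried into advice for later sites.

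The definitions also govern data capture. If the log keeps only one Yes or No per site-month, a Yes earned by a reach reply cannot later be separated from other contact, nor an aid download from, say, the download of an integration guide.

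**Working it through.** The article states no sample size, power or significance level for these regressions, so there is no figure to reproduce. The check traces the definitions and then sizes the effect under a null.

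**Step 1: algebra.** For a site, let p be true reach, r the fraction of months with a reply, and o the chance of other contact in a month, with p independent of r. Communications engagement as a frequency is r + (1 − r)o.

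- Silent months counted as zero use: measured reach ≈ p·r. Its covariance with the factor is (1 − o)·E[p]·Var(r), which is positive although p and r are unrelated.
- Replying months only: measured reach ≈ p, and the covariance is 0.
- Month-level analysis: every month with reported reach is scored Yes, so the factor is constant among those months. This follows from the definition and needs no simulation.

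For website engagement, let U be reported uses, D aid downloads and E eligible patients. If reach is (U + D)/E, D raises both the outcome and the predictor. If reach is U/E, D appears only in the predictor.

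**Step 2: simulation under the null.** From the document: up to 5 + 32 = 37 sites, site as the unit, factors scored by how often sites engage. Assumed:

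- 20 or 37 sites and 12 or 24 months;
- about 8 eligible patients per site-month;
- mean reply probability about 0.6, and o = 0, 0.3 or 0.6;
- aid downloads at 0.30 × a site propensity per eligible patient. At the median propensity, 1/(1 + e) = 0.269, this is 0.30 × 0.269 × 8 ≈ 0.65 downloads a month;
- 1,000 runs per scenario, site-level linear regression tested at two-sided 5%.

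| Factor and reach rule | Mean r | Significant, 20 sites | Significant, 37 sites |
|---|---|---|---|
| Communications, silent months = zero use | 0.55 to 0.74 | 76.1-98.4% | 97.2-100% |
| Communications, replying months only | −0.01 to 0.01 | 4.9-6.9% | 5.3-7.4% |
| Website, aid downloads added to reach | 0.26 to 0.28 | 20.6-23.1% | 34.3-39.8% |
| Website, reported uses only | 0.00 to 0.01 | 4.6-6.3% | 4.7-6.3% |

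A second null simulation used 37 sites, 24 months, 2,000 runs and a mean of 2 downloads per engaged month. It gave 65% for website engagement with downloads added, and 100% for communications engagement with silent months adding no uses. The website figure therefore spans about 21-65% and depends strongly on the assumed download rate.

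**Step 3: dashboard development.** Patient-reported outcomes exist only where a survey was collected. Matched by month, every respondent has the factor at Yes, so no coefficient can be estimated. As a site frequency it can vary, but sites with no surveys supply no outcomes and drop out.

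**The case against.** The strongest defence is that the stated design has a natural reading with no artefact. The site is the unit and factors are frequencies, so a site's reply rate varies even when reach uses only replying months, and the error rate is then near nominal. Sites determine eligibility and project staff have no access to site records. A silent month most naturally supplies neither numerator nor denominator, so counting it as zero use is not something the article describes. Nor does the article say that reported uses and online accesses are summed. The analysis is labelled exploratory, and handling of silent months may belong in an analysis plan not shown here.

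Most of this stands, and it makes the problem conditional. It does not remove the overlap: online access is listed as a source for reach, and the scoring rule does not exclude aid downloads or the reach reply.

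Three stronger readings are tempting and not supported:

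- A reader might infer that the communications coefficient must be either built in or inestimable. At site level with replying months only it is neither.
- A reader might infer that the patient surveys contaminate the reach regression. Surveys do not generate reach; their overlap is confined to the patient-reported-outcome models.
- A reader might infer that the second aim goes largely unanswered because resources lack factors of their own. Integration progress has its own factor, website comments can capture some forum activity, and contacts within the Collaborative are surveyed and separately regressed on reach. Asking for finer logs of videos or webinars is a wish for more data, not the correction of an error.

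**Conclusion.** The point holds as a conditional flaw in two of the six rated factors, and the overlap is partial: other contact, other downloads and comments also score Yes. Without any true effect, false-positive rates are about 21-65% for website engagement if aid downloads enter the numerator, and about 76-100% for communications engagement if silent months count as zero use. They are about 5-7% if reach uses only reported uses from replying months. The sizes rest on assumed reply, contact and download rates; the direction and the month-level constancy follow from the definitions.

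Dashboard development is a separate, smaller fault in the patient-level models. The descriptive reach percentage and the three quarterly factors (champion engagement, team engagement, integration progress) are not touched.

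**What to change.** 1. Score communications engagement on contact other than the monthly reach reply.
2. Score website engagement without conversation-aid downloads and click-outs.
3. For these regressions, compute reach from reported uses in replying months only, and treat months without a reply as missing, not zero. This is needed alongside items 1 and 2, because sites that reply may also make other contact, and sites that download aids may also download other material.
4. Drop dashboard development from the patient-reported-outcome models.

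The cost is a small change to the log sheet, which must separate types of contact and types of download. The redefined factors will be somewhat sparser, which gives up some precision.

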**Quarterly**		
Clinical champion engagement	High/intermediate/low	For example, **• Low** = lack of interest; **• High** = Evident interest and support
Team engagement	High/intermediate/low	For example, **• High** = attendance of team members at meetings **• Low** = no attendance of team members at meetings
EHR/telehealth/patient portal Integration progress	High/intermediate/low	For example, **• High** = engaging in at least one integration **• Intermediate** = interested by not complete **• Low** = not happening

##### Evaluation

We will calculate descriptive statistics summarizing the NoMAD survey results for each phase 1 site at the conclusion of the implementation period.

Separately, we will use the factors shown from Table 1 as variables in a linear regression analysis to explore which factors might be associated with high levels of patient reach (clinical championship, team engagement, communications engagement etc.) and therefore might predict future patient reach. For these regressions, patient reach will be the dependent variable and each implementation factor will be an independent variable. We will assess each item at the site level so that “site” will be the unit of analysis. We will control for patient demographics and other potential sources of site heterogeneity, if possible.

Additionally, we will conduct mixed-effects linear or logistic regression analyses to examine the association between these implementation factors and our patient-reported outcomes. We will conduct an analysis for each outcome while controlling for patient demographics as fixed effects. For this analysis, “patient” will be the unit of analysis but we will account for clustering at the site level as a random effect.

#### Maintenance

##### Data collection

During the project funding application, we developed a partnership with the American Society of Breast Surgeons (ASBrS) to initially recruit interested clinical sites and then serve as a willing candidate to sustain the SHAIR Collaborative and/or components of the SHAIR Collaborative. We will communicate regularly with dedicated team members from ASBrS to work on the sustainability strategy and all meetings will be documented by a project team member. One core promoter of sustainability is the open-access nature of the early-stage breast cancer Option Grids on the EBSCO website. Another will be the open-access online learning collaborative platform.

##### Evaluation

We will report our progress on sustainability plans with ASBrS at the conclusion of the project funding period.

### Data management

Patient reach data and implementation facilitating data will be tracked via spreadsheets and stored in a shared project folder. Survey data will be stored in the Dartmouth Qualtrics database, a HIPAA-compliant web-based data management system. Dartmouth project staff will not have access to the EHRs at any participating phase 1 or phase 2 sites. Our database management system is designed to comply with the ICH Good Clinical Practice guidelines. For statistical analysis, data will be downloaded and stored on an encrypted hard drive owned by Dartmouth College.

### Project management

We will use a community-based participatory research approach to ensure lasting and valuable partnerships with our variety of project stakeholders (clinical, research, patient, community, and organizational) [44–47].

We will hold quarterly steering group meetings with all key personnel and additional project members who advise on the project’s scientific and strategic direction using Zoom conferencing. The duties of the steering group will include supervising and monitoring study progress and providing feedback.

We will hold quarterly Community Advisory Board meetings that include all patient and stakeholder partners using Zoom audio conferencing. In these meetings, we examine project progress and materials and discuss relevant project items with a specific focus on the community perspective.

We will regularly engage with our phase 1 and phase 2 site contacts through various communication strategies guided by levels of engagement and feedback from the clinicians and other stakeholders. It is important to tailor communication methods to accommodate the busy schedules of clinicians and their teams. We will note these various communication strategies and their progression to determine which may be best for sustainability.

## Discussion

We are implementing evidence-based strategies for shared decision making about early-stage breast cancer surgery by creating and evaluating an online learning collaborative, the SHAIR Collaborative. The SHAIR Collaborative will be a group of clinical sites across North America implementing shared decision making by using two early-stage breast cancer conversation aids, called Option Grids. The SHAIR Collaborative will (1) reach early-stage breast cancer patients across diverse clinics in North America, (2) evaluate and visualize patient-reported outcomes, (3) contain up to 32 actively participating sites, (4) inform which factors of engagement affect implementation success (patient reach), and (5) potentially be sustained by the American Society of Breast Surgeons (ASBrS).

Early-stage breast cancer patients are not often involved in the decision making for their surgery to the extent they prefer, and patients and surgeons alike wish to have effective conversation aids, like the early-stage breast cancer Option Grid, implemented in future breast cancer care [2–7, 11]. Dissemination will take place across diverse clinical settings in North America. Scalability of the SHAIR Collaborative is an important factor to consider throughout dissemination and implementation; an open-access website with an easy-to-use server-side and our collaboration with ASBrS on sustainability plans will support scalability. One major benefit for scalability and sustainability is that the conversation aids will be updated and offered for free in perpetuity, eliminating an important barrier to access (cost). Additionally, other engagement factors and utilization of SHAIR offerings may inform the sustainability strategy and other future implementation projects.

One practical limitation in this project is the challenge of engaging with busy clinicians. It is important to be willing to tailor the communication strategy to our sites in order to improve engagement. There is also a balance between under- and over-communicating, making it important to focus on the necessary items (especially pertaining to sustainability) to cover with clinicians. Another practical limitation is the generalized nature of the Option Grid conversation aids. Feedback regarding the statistical content on Option Grids is often site-specific, so we consistently suggest to use the conversation aids flexibly, allowing for adaptations for individual patients. One major strength of this project is the support from ASBrS, ensuring better chances at sustaining the whole or parts of the SHAIR Collaborative when the project funding is over. The support from our community-based partnerships, especially patient partners, provides a strong and diverse stakeholder group ensuring all voices are heard, which may help with sustainability. Another strength is the SHAIR Collaborative platform itself—open-access, completely online, and ability to support sites from across North America. We are also using well-established frameworks throughout the creation, data collection, and evaluation of the project: Diffusion of Innovation, RE-AIM, Normalization Process Theory, and FRAME and FRAME-IS [25, 31, 40, 42].

We will participate in numerous dissemination activities through conferences and other communication platforms. We will also engage all project stakeholders in the dissemination of our project findings.

